### Study interventions

The study will not include any interventions or require any patient samples (e.g. blood / sputum / tissue).

### Study activities

Broadly, the activities involved in the research will include interviews with Cases and Controls during household visits, and a pre-FGD survey, FGD, and workshop with key stakeholders.

During Project 1, the project team will support BNMT district coordinators, community mobilisers, and community volunteers to do household visits to approximately 200 Cases with TB (100 diagnosed through ACF and 100 through PCF) recruited to WP3 of the IMPACT-TB project. People with TB will receive two household visits, the first during month three of TB treatment and the second visit during month six of TB treatment (to correspond with treatment completion). For controls, a single household visit and interview will be done. The interviews will be structured (see Project 1 Interview,
*Extended data*)
^29^ and gather data on: i) socioeconomic position, evaluated by a multi-dimensional poverty score
^6,
9,
13,
15^ assessing dwelling characteristics, assets, and access to amenities; ii) household structure, including distribution of age, sex, and employment of household members; iii) food expenditure and security; iv) costs of engaging with TB care including direct costs (e.g. medicines, clinic visits, food, and travel) and indirect costs (e.g. lost income), which will be evaluated using an adapted version of WHO’s TB Patient Costs Survey integrated into the interview
^22,
23^; v) coping strategies including dissaving (e.g. selling assets), schooldays lost, and temporary income-generating activities; vi) TB-related knowledge including understanding of transmission, prevention, and treatment of TB; vii) psychosocial situation evaluated through questions relating to social capital, quality of life, and stigma (Controls without TB will not be asked any questions about the impact that having TB disease has on their psychosocial situation); and viii) access and uptake of existing social protection schemes (whether TB-specific or TB-inclusive) and support for TB-affected households, evaluated through use of both closed ranking and open free-text questions to establish what socioeconomic and other support people with TB and their households receive or would like to receive.

Prior to implementation of household visits, the questionnaire will be translated from English into Nepali and then back-translated into English. It will be assessed by members of the study team and BNMT implementation staff before being piloted in approximately 10 patients. The questionnaire may subsequently be refined and questions deleted or added, depending on the pilot outcomes.

In addition to the above, Cases’ TB treatment outcomes will be collated from NTP and IMPACT-TB data and their association with interview responses analysed. This will provide an exploratory analysis of the association of socioeconomic position, socioeconomic impact of having TB, and TB treatment outcomes. A comparison of the socioeconomic position of households of Cases and Controls will also be made.

Project 2 will use and develop mixed methods research techniques
^10–
15^ to conduct a pre-FGD survey, FGDs, and workshop with approximately 40 key stakeholders in Nepal to identify the socioeconomic impact, barriers and facilitators to accessing and engaging with TB diagnosis and care. To inform the design of the FGDs and workshop, we created a conceptual framework for the barriers and facilitators to TB diagnosis and care, which was adapted from a World Health Organisation framework for medication adherence (
Figure 3)
^33^.

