**Figure 1. f1:**
[figure not shown]
**a**) Catastrophic costs incurred by intervention (n=135) and control (n=147) TB-affected households of Callao, Peru.
**b**) Preventive therapy initiation in household contacts of intervention (n=206) and control (n=204) TB-affected households of Callao, Peru.
**c**) TB treatment success in patients from intervention (n=135) and control (n=147) TB-affected households of Callao, Peru. Part
**a**) has been reproduced with permission from Wingfield
*et al.*
^13^ Parts
**b**) and
**c**) have been reproduced with permission from Wingfield
*et al.*
^15^.

However, despite these encouraging findings, Peru is a middle-income country with a strong TB program and existing national cash-transfer schemes. To make this research replicable and applicable in diverse settings, interventions similar to those in Peru need to be adapted to other country contexts, especially low-income countries (LICs) with less developed social protection schemes and high TB burden. One such country is Nepal.

The estimated incidence of TB in Nepal is 154/100,000 people with 45,000 cases of TB being notified. Amongst these cases, there were 6,800 TB-related deaths. Multi-drug resistance (MDR) rates were 2.2% in new cases and 15% among retreatment cases. Importantly, despite good treatment success rates overall of more than 90% reported in Nepal, there remain shortcomings in TB care: treatment success rates were 70% for patients with MDR-TB and only 9% for those with HIV-TB co-infection; and accessibility of TB care remains low with treatment coverage of 70%
^16^.

The poor treatment coverage in Nepal may, in part, be due to the financial impact on TB-affected households, which is estimated to be high
^17^. Responding to this estimated burden, the Nepal National TB Programme (NTP) national strategic plan for 2016–2021 identifies provision of a support package to TB-affected households (specifically targeting MDR-TB-affected households) as a priority aim for the country with the goal of reducing catastrophic costs. There is currently limited evidence concerning the potential acceptability, impact, or cost-effectiveness of such a package, with which to inform and guide this policy decision. A cohort study has suggested that, during their illness, TB patients in Nepal experience decreased income and the total costs of accessing free TB treatment equate to nearly one quarter of annual household income

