### Study population

***Participant identification, recruitment and follow-up***. During Project 1, approximately 200 people with TB (cases) consecutively recruited to Work Package 3 (WP3) of IMPACT-TB (Health Economic Analysis) in the four study sites will be further recruited to this study. 100 of these cases will have been diagnosed through ACF and 100 diagnosed through PCF. Whilst attending the NTP TB clinic, these people with TB will be invited to participate in this mixed-methods research with a separate written, informed consent (see Project 1 Interview Patient Consent Form,
*Extended data*)
^29^. During months three and six of their TB treatment, household visits will be conducted by BNMT project staff including community mobilisers.

Concurrently, 100 people without TB from the study sites (controls) will be invited to participate with written, informed consent (see Project 1 Interview Healthy Control Consent Form,
*Extended data*)

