Project 1 inclusion criteria for Cases included: being a person with TB notified to the NTP and recruited to WP3 of the IMPACT-TB study; being aged 18 years or above; and giving verbal and written informed consent to participate. Project 1 exclusion criteria for Cases included: being under 18 years of age; being a person with TB not notified to the NTP and/or not recruited to WP3 of the IMPACT-TB study; being a person with TB notified to the NTP but with a recorded domiciliary address outside of the study site districts; and being unable or unwilling to give written and/or verbal informed consent to participate.

Project 1 inclusion criteria for Controls included: being 18 years or above with primary residence in the study site communities; not currently known to be a person with TB or have a member of the household currently known to be a person with TB (e.g. not diagnosed or notified or receiving TB treatment); and giving verbal and written informed consent to participate. Project 1 exclusion criteria for Controls included: being under 18 years of age; not having primary residence in the study site communities; known to be a person with TB or have a household member with TB currently (e.g. diagnosed and/or notified and/or receiving TB treatment); and being unable or unwilling to give verbal and written informed consent to participate. 

To generate the population for Project 2, a literature review and desk-based scoping review will identify a list of key in-country stakeholders from Nepal from diverse groups including: civil-society representatives; community leaders; and TB healthcare professionals including NTP managers and multi-disciplinary staff. Approximately 50 stakeholders will be selected through purposive sampling and invited to participate in: a pre-FGD survey, FGD, and a one-day workshop. A subset of purposively sampled TB patients recruited to Project 1 (including those with multi-drug resistant TB) will be among the stakeholders invited to participate.

Project 2 inclusion criteria include: being aged 18 years or above; belonging to a stakeholder group as defined above and/or identified during scoping exercise; and being able and willing to provide verbal and written, informed consent. Exclusion criteria for Project 2 are not meeting the inclusion criteria and/or being a person with TB who has not yet taken two weeks of TB treatment or is otherwise considered to still be infectious (e.g. MDR-TB with positive sputum smear or culture).

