### Study status

Data collection for Project 1 during household visits began in May 2018 and is nearly complete at the time of writing with only TB treatment outcome data still being collected. Data collection for Project 2 during pre-FGD surveys and FGDs began in August 2018 and was completed in July 2019. The national workshop with key stakeholders was conducted on 11 and 12 September 2019 in Kathmandu, Nepal.

Data analysis, write-up, and dissemination of findings will begin in February 2020.

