## Conclusions

This mixed-methods study will fill this existing evidence gap by examining the costs of accessing TB care at a household level through longitudinal application of an adapted WHO TB Patient Costs Survey throughout TB treatment. This data will be enriched by collecting complementary data on household socioeconomic position, coping strategies, food insecurity, TB knowledge, social capital, and quality of life. The findings will then feed into a short survey and semi-structured FGDs with key stakeholders in Nepal to consider, at a local, regional, and national level, what are the leading barriers and facilitators to accessing and engaging in TB care, and what might be the most locally-appropriate interventions to address the socioeconomic impact of having TB disease.

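### The month-six visit is equated with treatment completion for every case, yet Project 1 includes MDR-TB patients and no later cost interview is described

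*Protocol article*

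**What the plan says.** Study population sets the timetable: "During months three and six of their TB treatment, household visits will be conducted by BNMT project staff including community mobilisers". Study activities repeats it for "approximately 200 Cases with TB (100 diagnosed through ACF and 100 through PCF") and ties the last interview to the end of treatment: "the second visit during month six of TB treatment (to correspond with treatment completion"). Neither section makes an exception by regimen or mentions a later household visit.

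The Conclusions describe the cost measurement as "longitudinal application of an adapted WHO TB Patient Costs Survey throughout TB treatment".

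The Project 1 criteria for cases contain no drug-resistance exclusion. The description of the Project 2 sample confirms that such patients are enrolled: "A subset of purposively sampled TB patients recruited to Project 1 (including those with multi-drug resistant TB").

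Treatment outcomes are to come from programme and IMPACT-TB data (Study activities), and case data are to be linked to the National TB Programme register (Data collection and management). The Data analysis and statistical plan refers the analysis of household income and expenditure to the WHO patient cost survey methods. It replaces zero or missing amounts by category means, and states no rule for costs that arise after the last interview.

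**The concern.** Three statements do not fit together: the last cost interview is at month six for everyone, that interview corresponds with completion, and the cohort includes MDR-TB patients. If some of them are still on treatment at month six, what they spend and the income they lose afterwards is not observed. The claim of coverage throughout treatment is then untrue for them.

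The group affected matters for the study's purpose. The Introduction reports that the national strategic plan proposes a support package "specifically targeting MDR-TB-affected households", with the goal of reducing catastrophic costs, and says that evidence to guide that decision is limited. A cost figure that stops early understates the burden in the households that the policy singles out. It would also feed into the planning of the later trial.

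**Working it through.** The article states no figure on this point, so there is nothing to reproduce. The check is one of scale.

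**Inputs from the documents**
- About 200 cases (Study activities).
- Last cost interview at month six (Study activities).
- National MDR rates (Introduction, text after Figure 1): "Multi-drug resistance (MDR) rates were 2.2% in new cases and 15% among retreatment cases".

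**Inputs assumed, because the documents do not give them**
- Retreatment share r among the cases: 0 to 20%.
- MDR-TB treatment length T: 9 to 24 months.
- Even monthly costs, the same for MDR-TB and other cases; other cases finish at month six; nothing is extrapolated.
- National MDR rates apply to this sample.

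**Step 1: how many cases.** MDR share f = (1 − r) × 0.022 + r × 0.15.
- r = 0: f = 0.022, and 200 × 0.022 = 4.4 cases.
- r = 0.10: f = 0.0348, and 200 × 0.0348 = 7.0 cases.
- r = 0.20: f = 0.0476, and 200 × 0.0476 = 9.5 cases.

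The chance of at least one MDR-TB case among 200 is 1 − (1 − 0.022)^200 = 98.8% at the lowest share, and higher at the others. The article in any case presupposes some.

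**Step 2: how much of one household's treatment-phase cost is seen.** Captured share = 6/T.
- T = 9: 6/9 = 67%.
- T = 12: 6/12 = 50%.
- T = 18: 6/18 = 33%.
- T = 24: 6/24 = 25%.

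**Step 3: effect on the mean over all cases.** Set the six-month cost to 1. The true mean is (1 − f) + f × T/6 and the observed mean is 1. Understatement = 1 − 1/[1 + f × (T/6 − 1)].
- T = 9, f = 0.022: 1 − 1/1.011 = 1.1%.
- T = 12, f = 0.0348: 1 − 1/1.0348 = 3.4%.
- T = 18, f = 0.0348: 1 − 1/1.0696 = 6.5%.
- T = 24, f = 0.0476: 1 − 1/1.1428 = 12.5%.

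These percentages concern treatment-phase cost only. Costs before or at diagnosis come before month six and are not cut off, so the relative effect on a total that includes them would be smaller.

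**The case against.** The strongest reply is that this is a condensed article. It refers income and expenditure analysis to the WHO survey methods, and the handling of unfinished treatment may stand there, in the adapted questionnaire or in an analysis plan that is not shown. The study is exploratory and mainly descriptive, the affected cases are few, and the documents never say that MDR-TB treatment outlasts six months. On that view, a clarifying clause would be enough.

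Much of this stands, and it limits what may be inferred:
- **That month-six costs are counted as complete.** A reader might infer this from the words about completion. No section says so, and none says that such costs are censored or extrapolated.
- **That truncated costs are tested against the 20% threshold.** That figure appears in the Introduction as the WHO definition of catastrophic costs. The analysis section does not specify the test.
- **That Study status proves continued treatment.** It says that Project 1 data collection "is nearly complete at the time of writing with only TB treatment outcome data still being collected". Outcomes come from programme records, so a delay in the register explains this equally well.
- **That up to 30 cases are affected** (200 × 0.15). This would need every case to be a retreatment case, which nothing in the article suggests.
- **That a household's whole cost shrinks in proportion to 6/T.** Only treatment-phase cost can be cut off.
- **That the comparison of active with passive case finding is distorted.** This needs the share still on treatment to differ by route, and the documents give no sign either way.

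What the reply does not remove is the inconsistency itself. The timing of the last interview and its equation with completion are stated design features, not details left to another document. An analysis rule elsewhere could extrapolate later costs, but could not turn them into collected data.

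**Conclusion.** The concern holds as a conflict between stated design features. The article equates month six with completion for all cases and claims cost coverage throughout treatment, while enrolling MDR-TB patients and describing no later cost interview. For any case still on treatment at month six, later costs are not collected and that household's cost is understated unless it is extrapolated.

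The effect on the pooled mean is small to moderate, about 1% to 12.5%, and the upper end needs both the longest assumed treatment and the highest assumed MDR share. The effect within the roughly 4 to 10 MDR-TB households is large, with about a third to three quarters of treatment-phase cost unseen. Both ranges rest on the assumed treatment length, even monthly costs, the assumed retreatment share and the use of national MDR rates for this sample. If every case had finished by month six, the bias would be nil and only the wording would need attention.

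**What to change.** 1. Reconcile the statements in Study population, Study activities and Conclusions. Qualify the remark that month six corresponds with completion, and the claim of coverage throughout treatment, for cases who have not finished.
2. Obtain each case's treatment end date, or status at the second visit, through the register linkage already planned.
3. Flag every case not finished at the second visit and label those figures as costs to month six.
4. Report mean costs, and any catastrophic-cost proportion if one is presented, for all cases together and separately for finished and unfinished cases. Do not drop unfinished cases, since that would remove the households of most policy interest.
5. Add a sensitivity analysis that extrapolates the unfinished cases' costs, with its assumptions stated.

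The cost is one extra variable, a few table rows and one sensitivity analysis. No new visits are needed and no clinical procedure changes. The downside is that the unfinished subgroup will be small and its estimates imprecise, so they should be shown with confidence intervals and read as descriptive.

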**Figure 3. f3:**
[figure not shown]
Conceptual framework: the barriers and facilitators to TB diagnosis and care The central circle, which contains dimensions of medication adherence adapted from the World Health Organization
^32^, is surrounded by the five main categories of relevant potential interventions. The factors that may promote access to and engagement with TB services (facilitators) are shown in green boxes and factors that may threaten access and engagement (barriers) are shown in white boxes. Therapeutic alliance refers to strong provider-patient relationships. Although Project 2 would gather data on all five dimensions, the psychosocial and social protection dimensions were perceived by the project team to be most pertinent to development of the socioeconomic intervention and were selected for further focus and discussion during Project 2’s workshop.

A short individual pre-FGD survey (see Project 2 Survey,
*Extended data*)
^29^ will be provided to participants prior to the initiation of an FGD. The survey will detail: participants’ demographics; the stakeholder group to which the participant belongs; and their opinions on community, patient, health system, existing social protection schemes, and wider obstacles to achieving successful TB treatment outcomes.

The FGDs will be semi-structured and incorporate open-ended questions concerning barriers and facilitators to accessing and engaging with TB care in Nepal, and existing platforms and potential opportunities to mitigate these barriers including social protection schemes (see Project 2 Focus Groups,
*Extended data*)
^29^. The FGDs will be conducted with separate groups of approximately eight key stakeholders. Stakeholders will be invited to participate according to their background (e.g. people with TB will be asked to participate in one FGD, and TB healthcare professionals will be asked to participate in another separate FGD). Towards the end of each FGD, participants will be asked to privately rank the top three most important barriers or facilitators to accessing TB diagnosis and care identified by the group during the FGD, and these responses will be collated for each FGD and across FGDs. The FGDs will be moderated by members of the project team trained in qualitative methods including conducting FGDs. The discussions will be audio recorded in Nepali language, translated into English, and back-translated by a translator who is not part of the project team. Each FGD group will be asked to elect a representative to feed their group’s outputs back at the subsequent workshop.

The final activity in Project 2 will be a one-day workshop bringing together the 40 key stakeholders (see Project 2 Workshop,
*Extended data*)
^29^. The morning section of the workshop will consist of interactive presentations from the project team and stakeholder group representatives (including leaders of national social protection schemes in Nepal), and discussions exploring and validating the barriers and opportunities identified during the pre-FGD survey and interviews during FGDs. The afternoon section of the workshop will consist of multi-sectoral working groups (≤10 diverse stakeholders) developing a shortlist of potential socioeconomic interventions for TB-affected households in Nepal. The shortlist is not intended to consist of defined, unalterable packages, which are immediately ready for trial implementation. Rather, the potential interventions selected are intended to consist of what stakeholders perceive to be key elements or ingredients of psychosocial and economic support for TB-affected households, which are feasible and locally-appropriate to the Nepalese context. The interventions will be presented to the group including strengths, weaknesses, and potential sources of funding for implementation.

The activities involved in this research form part of a process to develop and evaluate a complex, socioeconomic support intervention. In line with the Medical Research Council’s guidance on process evaluation of complex interventions, we developed a logic model to illustrate the developmental stages of the intervention (
Figure 4)
^33^.

**Figure 4. f4:**
[figure not shown]
Logic model for research in Nepal to develop a locally-appropriate socioeconomic support intervention for TB-affected households. Abbreviations: CSOs = Civil Society Organisations; NGOs = Non-governmental organisations; NTP = National Tuberculosis Programme; WHO = World Health Organisation; SPARKS = Social Protection Action Research and Knowledge Sharing network (
www.sparks.ki.se)

This Wellcome research will aim to achieve the short-term outcomes described in the logic model. If follow-on funding is successfully obtained, the process to develop and implement the intervention and achieve the long-term outcomes will continue beyond this Wellcome research. This will include adaptation, piloting, and then large-scale randomised trial evaluation of the refined intervention.

